## Background

Work-related musculoskeletal disorders (WRMDs) are a group of functional and mechanical disorders, often caused by overuse or inadequate use of the musculoskeletal system during work [1–3]. Muscles, tendons, fascia, nerves, joint and bones can be affected, and the result is fatigue, decreased performance at the workplace, temporary disability and absenteeism with economic consequences [4]. WRMDs are the second major cause of sick pay benefits in social security [5] and its prevalence has been increasing [1].

The most affected areas by WRMDs are neck, upper extremity, and low back [6–8]. Neck and upper extremity disorders can be divided into specific conditions with clear pathology and diagnosis, such as carpal tunnel syndrome, or non-specific conditions, which are defined by the location of symptoms, with unknown or imprecise physiopathology, such as neck strain syndrome [9].

Risk factors at the workplace related to neck and upper extremity symptoms include physical factors (harmful postures, repetitive tasks and static contractions), organizational factors (excessive work and absence of breaks), and psychosocial factors [6, 9–12]. Many tools have been developed and validated for the work ergonomics assessment. They aim to facilitate the survey of data regarding the various demands and workplace setting, postures assumed during professional activities, the perception of the worker regarding symptoms and muscle fatigue, and also to identify and classify the risk factors for the development of WRMDs [13–15].

In order to reduce WRMDs many companies have been investing more in prevention programs with a multidisciplinary approach for the promotion and maintenance of health, providing safer working conditions [16–18], adequate ergonomics [19] and workplace exercises [1, 9, 20]. Workplace exercises consist of specific activities performed during the working time. They usually have a short duration, with both preventive and therapeutic approaches, avoiding overloading or leading the employee to fatigue. It is a physical activity based on exercises to compensate repetitive movements, the absence of movement, or uncomfortable postures assumed during the working period [21].

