### Participants

The participants of this study will be employees of a tertiary hospital, from any section, with any complaints of pain or discomfort in the upper extremity during the past 12 months. Potential subjects will be recruited by verbal invitation, posters and institutional cell phone messages. Inclusion and exclusion criteria are described in Table 1. All participants will sign a written informed consent form before participating.

**Table 1 Tab1:** The Inclusion and Exclusion criteria description

Inclusion Criteria	Exclusion Criteria
• > 18 years old; • both sexes; • provide written consent; • workers who have musculoskeletal complaints in the past 12 months in the cervical region, shoulder, elbow, wrist or hand and/or fingers, without a clinical diagnosis; • workers who are not away from their professional activities.	• pregnancy; • congenital spinal abnormality and significant musculoskeletal deformities (such as amputation, dysmetria); • severe cervical spine disorders, postoperative conditions in the neck or upper limb region; • uncontrolled cardiovascular disease, cardiac arrhythmia, angina or related symptoms, and postural hypotension or other contraindication for physical exercise; • workers who engage in some form of regular exercise, which involves strengthening exercises and muscle resistance; • workers who have diagnosis of musculoskeletal dysfunction of the upper extremity and are undergoing physiotherapy treatment.

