### Randomization

Employees who agree to participate will be randomized in a 1:1 ratio by a random allocation sequence by concealment envelopes in two parallel groups: control group (CG) and workplace exercise group (WEG).

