### Statistical approach

An investigator will receive the encoded data and perform the statistical analysis entered into a database Excel spreadsheet. The Kolmogorov-Smirnov test will be used to verify the normality distribution of the data. Descriptive statistics (frequencies, means, standard deviation, confidence interval) will be used to analyze the sociodemographic characteristics of the participants. The significant statistical difference between the outcome groups will be analyzed by the T test of independent samples to compare the means at the baseline and after 12 weeks of intervention, using as outcome variables the numeric pain scale, the mean isokinetic scores of peak torque and work, the patient self-reported questionnaires, with 95% confidence interval, *p* < 0.05. Responsiveness values for interventions to changes in clinical significance will be defined to score the minimum clinically important difference [56]. The Cohen Index will be defined to calculate the effect size, considering 0.3 low, 0.5 moderate and 0.8 high effect [57]. The association between the variables will be analyzed through the construct validity by the hypothesis tests, which determine the convergent and discriminant validity [58, 59]. It is expected that there will be moderate inverse correlation between pain and muscle strength production, moderate correlation between strength production and functionality and strong to moderate correlation between strength production and fatigue endurance. The statistical program SPSS Statistics 20.0 will be used for all analyses [57, 60].

The confounding factors that could be accounted for in the statistical plan and potential to bias even with the randomization process are: occupations will be analyzed together for comparations between control and intervention groups, before and after the intervention but not in subgroups by level of activity load; and intention-to-treat analysis will be performed including data for the noncompliance volunteers, in exception for dropout cases due to loss of follow-up [61].

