## Discussion

The WMSDs impair occupational activities, reducing productivity at work and increasing absenteeism. They also impact activities of daily living, reducing the quality of life in general. Besides, they generate economic consequences [4, 62]. Workplace exercise is an available therapeutic resource that has been widely used to minimize work-related complaints of pain and discomfort [1, 2, 9, 29]. Its benefits for workers’ health and for the company are already well known in some worker populations, but it is not yet well-established which exercise modalities would have the greatest benefit for workers.

Therefore, the purpose of this clinical trial is to evaluate the effects of a specific resistance exercise program associated with muscle stretching for the upper extremity and cervical region during the working day and compare them to just ergonomic guidance in reducing fatigue and complaints perceived by workers at a university hospital. We hypothesize that workers who receive the workplace exercise intervention will experience decreased pain, fatigue, dysfunction and better perceived long-term work capacity.

The results of this study will bring more evidence about the benefit of a specific resistance exercise program for workers with upper extremity complaints. Possible challenges for this study will include difficulties with participants recruitment and loss of participants for follow-up. To address these challenges, we will make the study widely known at the hospital in order to reach about all the professionals of the hospital in the different support areas such as maintenance, hygiene and cleaning and hospital nutrition, as well as employees in the administrative sector and health professionals.

The choice of the intention-to-treat analysis could reflect the reality of clinical practice in that workers often do not follow ergonomic or exercises instructions and sometimes take up a completely different approach from the one recommended. The limitation issue is that if the adherence is poor, then the results of the study may not be generalized well to workers who do comply with the intervention based on exercises in the intervention group and the ergonomic approach for both groups [63].

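### Occupation is named as a possible source of bias, but the pooled, unadjusted t test does nothing to account for it; the cost is some precision, not validity

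*Protocol article*

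**What the plan says.** All places are in the protocol article.

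- **Who is recruited.** Under Participants, eligible workers are "employees of a tertiary hospital, from any section". The Discussion says that recruitment will reach "different support areas such as maintenance, hygiene and cleaning and hospital nutrition, as well as employees in the administrative sector and health professionals".
- **Why jobs matter.** The Background states: "Risk factors at the workplace related to neck and upper extremity symptoms include physical factors". It goes on to organisational and psychosocial factors.
- **What is recorded.** Demographic information, collected at baseline, includes occupation and work task.
- **Allocation.** Under Randomization, workers are "randomized in a 1:1 ratio by a random allocation sequence by concealment envelopes in two parallel groups". No stratification factor is mentioned, and none is ruled out.
- **Analysis.** Under Statistical approach, the arms are compared by an independent-samples t test with no covariate. A later paragraph opens "The confounding factors that could be accounted for in the statistical plan and potential to bias even with the randomization process are" and gives occupation first. The handling follows at once: "occupations will be analyzed together for comparations between control and intervention groups". A breakdown by how demanding the job is gets set aside in the same sentence: "but not in subgroups by level of activity load".

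**The concern.** The paragraph raises a problem and then states a handling that does not address it. Pooling all occupations gives a valid overall comparison. It does not correct for one arm having, by chance, more workers in heavy jobs, and it leaves the variation between jobs in the error term. This handling is written in the article, so it is not a detail left to an analysis plan that is not shown.

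If pain, strength or fatigue at 12 weeks differs between job types, an uneven job mix moves the estimated treatment difference. A reader who sees such an imbalance in the baseline table would then have no prespecified adjusted result to turn to. The variable needed is already being collected.

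**Working it through.** **Inputs**
- From Sample size calculation: effect size d = 0.5, power 80%, alpha 0.05 (taken as two-sided), 75 per group, 166 in total with 10% loss.
- Assumed, because the article gives no figure: R², the share of outcome variance explained by occupation, 0.05 to 0.10 (wider range 0.02 to 0.30); and p, the share of workers in one job category, 30 to 50%.

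**1. The plan's own figure.** n per arm = 2(1.960 + 0.842)²/0.5² = 62.8, so 63 (64 with the t distribution). The stated 75 is not reproduced from the stated inputs. At 75 per arm, power is Φ(0.5·√(75/2) − 1.96) = 86.5% (86.0% with the t distribution). The loss step is close: 150/0.9 = 166.7 against 166. This mismatch is a separate matter; 75 per arm is used below as the planned analysed size.

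**2. Chance imbalance in job mix without stratification.** SD of the between-arm difference in a category's share = √(2p(1−p)/n).
- 83 per arm randomised: p = 1/2 gives 7.8 percentage points, 95% limits ±15. p = 1/3 gives 7.3 points, limits ±14.
- 75 per arm analysed: p = 0.5 gives limits of ±16 points, and p = 0.3 gives ±15.

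**3. Effect on the treatment estimate and on power.** In outcome SD units, the SD of the chance shift due to occupation is √(2R²/n). Power after adjustment is Φ(0.5·√(75/2)/√(1−R²) − 1.96).

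| R² (assumed) | SD of shift, 75 per arm | 95% limits | Power at 75 per arm if adjusted | n per arm for 80% power |
|---|---|---|---|---|
| 0 | 0 | 0 | 86.5% | 63 |
| 0.02 | 0.023 | ±0.045 | 87.1% | 62 |
| 0.05 | 0.037 | ±0.07 | 88.1% | 60 |
| 0.10 | 0.052 | ±0.10 | 89.8% | 57 |
| 0.20 | 0.073 | ±0.14 | 92.8% | 51 |
| 0.30 | 0.089 | ±0.175 | 95.5% | 44 |

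**4. Is the shift already in the standard error?** Yes. The unadjusted 95% half-width is 1.96·√(2/75) = 0.320 SD. After adjustment it is 0.320·√(1−R²), which is 0.312 SD for R² = 0.05 and 0.304 SD for R² = 0.10. For R² = 0.05 the parts recombine: √(0.312² + 0.072²) = 0.320. The unadjusted interval therefore covers the imbalance honestly, and adjustment only narrows it.

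**The case against.** The strongest case against is that an unadjusted t test in a randomised trial is valid. Job-mix imbalance is random, so the estimate is unbiased on average, the type I error holds, and step 4 shows that the standard error already includes the imbalance. The gain from adjustment is modest, rests on an assumed R², and is smaller than the slack in a sample size of 75 where 63 or 64 would do. All of this stands, and it limits the point to one of precision.

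Other parts of the objection:

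- **Allocation.** A reader might infer that the envelopes form a single unstratified list. The article does not show this. It is a condensed account, and its silence does not settle whether allocation is stratified.
- **Subgroups.** Declining subgroup analyses by activity load is a reasonable choice at this size. Covariate adjustment needs no subgroups, so the choice does not answer the point.
- **Change scores.** The Abstract can be read as comparing change from baseline to 12 weeks, which would remove stable job differences. Differences between jobs in the change itself would remain, and R² then refers to the change.
- **Other routes.** Tailored workplace advice goes to both arms, and attendance at break-time sessions arises after randomisation. Neither is baseline confounding, so neither supports the point.
- **Categories.** The areas listed in the Discussion describe recruitment outreach and are not defined strata. Broad job families may be only a rough proxy for load.
- **Wording.** The sentence on confounding factors is hard to parse and speaks of potential bias. It should not be read as saying that bias is expected.

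**Conclusion.** The point holds as a minor improvement to the analysis. The Statistical approach section names occupation as a possible source of bias, then fixes a pooled, unadjusted comparison that does not account for it, although the variable is recorded at baseline.

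With 75 per arm and an assumed R² of 5 to 10%, the exposure is a chance shift of about ±0.07 to ±0.10 SD at the 95% limits, against a planned 0.5 SD. Power would rise from 86.5% to about 88 to 90%. If occupation explains only 2% of the variance, the gain is negligible; at 30% it would be substantial. The article gives no figure to choose between these.

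A reader might infer that the trial is expected to be biased by occupation, or that its test would be invalid. The documents do not support that: with proper randomisation the imbalance is a matter of chance and the type I error is preserved. That assurance concerns the arms as randomised. The plan leaves participants lost to follow-up out of the analysis, but nothing in the article says that loss will differ by job, so the point does not rely on it.

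**What to change.** In Statistical approach, replace the sentence that pools occupations with a prespecified between-group linear model (ANCOVA) that includes a small number of occupation categories as a baseline covariate. Define the categories before unblinding, and state that no subgroup analyses by occupation or activity load will be done.

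The cost is a few degrees of freedom and the work of fixing the categories in advance. With three categories, for example, 2 of the 148 error degrees of freedom at 75 per arm are used. No new data are needed.

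Stratifying the envelopes by the same categories is optional, and only if enrolment has not begun. If allocation is or becomes stratified, the stratum must enter the model. Keeping the unadjusted t test would make it conservative: the type I error is 2(1 − Φ(1.96/√(1−R²))), about 4.4% for R² = 0.05 and 3.9% for R² = 0.10.

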## Methods

### Trial design

This will be a prospective randomized controlled trial with concealed allocation by using opaque, sealed envelopes consecutively numbered and included each group’s name and deviation from the intention-to-treat analysis [30]. The study was designed according to the Consolidated Standards of Reporting Trials - CONSORT guidelines [31] for randomized clinical trials and following the standard protocol items for randomized interventional trials (SPIRIT) [32]. Participants will be randomized to receive either ergonomic guidance alone or ergonomic guidance and workplace strengthening exercises (Fig. 1).

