## Data analysis

### Sample size calculation

The a priori sample size calculation was performed by GraphPad Statemate™, with power of 80%, effect size of 0.5 and alpha level of 0.05, based on the Numeric Pain Rating Scale and the isokinetic scores of the mean peak torque of the abduction movement in the scapular plane [54]. Seventh five participants will be needed per group. A total of 166 participants with pain or discomfort complaints of upper extremity who meet the inclusion / exclusion criteria and consent to participate will be included in the study, considering 10% sample size loss and analysis per intent to treat [30, 55].

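### The analysis called intention-to-treat excludes everyone lost to follow-up, so it is an available-case analysis as randomised; the label and the rule need to be reconciled and the missing data handled

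*Protocol article*

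**What the plan says.** The protocol article describes the analysis population in four places.

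- Statistical approach gives the operative rule: "intention-to-treat analysis will be performed including data for the noncompliance volunteers, in exception for dropout cases due to loss of follow-up".
- Sample size calculation reaches 166 participants "considering 10% sample size loss and analysis per intent to treat", with no exception mentioned.
- Trial design refers to a "deviation from the intention-to-treat analysis" and does not say what it is.
- The Discussion defends the approach, again without the exception: "The choice of the intention-to-treat analysis could reflect the reality of clinical practice".

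The section on secondary outcome measures says that primary and secondary outcomes are taken at baseline and at 12 weeks. There is therefore one post-baseline assessment. The named test is the independent-samples t test. The article mentions no imputation, no likelihood-based model and no sensitivity analysis for missing outcomes, and its stated rule for dropouts is exclusion.

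**The concern.** This is a stated rule that fixes who is analysed, so it is more than a detail left for a later document. An intention-to-treat label tells the reader that the comparison rests on all randomised participants. The rule does not deliver that, and a reader who sees only the sample size section or the Discussion would not know.

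What is at stake is the comparability that randomisation gives. If those who leave differ in outcome from those who stay, and this differs between arms, the remaining groups are no longer comparable. Unequal loss is plausible here. Only the workplace exercise group is asked to attend three sessions a week for 12 weeks (3 × 12 = 36 sessions), participants are not blinded, and pain is a primary outcome. The Discussion itself expects loss to follow-up, and the measure it offers is publicity in the hospital, which helps recruitment more than retention.

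**Working it through.** **The plan's own figures.** The inputs are "with power of 80%, effect size of 0.5 and alpha level of 0.05", 75 per group, a total of 166, allocation 1:1 and 10% loss.

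- The allowance for loss reproduces: 75 × 1.10 = 82.5, rounded up to 83 per group, and 2 × 83 = 166. (Dividing instead gives 75/0.90 = 83.3, so 84 per group and 168 in all.)
- The 75 per group does not follow from the stated inputs, which give 64 per group for a two-sided t test. That is a separate matter and does not affect this point.
- After 10% loss, 166 × 0.90 = 149.4, or about 75 per arm. The inflation thus restores the intended number of completers. It does nothing about which participants are missing.

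**Who is analysed.** With one post-baseline visit, a t test needs a 12-week value. This is so whether it is run on 12-week means (Statistical approach) or on the change from baseline (Abstract). Setting this beside the exclusion rule gives:

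- stops exercising, attends at 12 weeks: kept, in the assigned arm;
- lost before 12 weeks: removed.

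The set is therefore available cases as randomised. It is neither per-protocol nor all randomised.

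**Bias formula.** In one arm let p be the share lost and g the amount, in SD, by which those lost are worse than completers. The mean over all randomised is (1 − p) × completers + p × lost. Completers therefore look better than the whole arm by p × g. Between arms:

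bias toward exercise = p_WEG × g_WEG − p_CG × g_CG,

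where WEG is the exercise group and CG the control group.

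**Illustrations.** All values of p and g are assumed, because the article gives none by arm. False-positive rates are two-sided, by normal approximation, with 83 randomised per arm.

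| Loss WEG / CG | Gap g | Bias (SD) | Share of 0.5 | False-positive rate |
|---|---|---|---|---|
| 15% / 5% | 0.5, both arms | (0.15 − 0.05) × 0.5 = 0.05 | 10% | 6.1% |
| 15% / 5% | 1.0, both arms | (0.15 − 0.05) × 1.0 = 0.10 | 20% | 9.4% |
| 20% / 5% | 0.5, both arms | (0.20 − 0.05) × 0.5 = 0.075 | 15% | 7.3% |
| 10% / 10% | same in both arms | 0 | 0 | 5.0% |
| 10% / 10% | 0.5, WEG only | 0.10 × 0.5 = 0.05 | 10% | 6.1% |
| 10% / 10% | 0.5, CG only | −0.10 × 0.5 = −0.05 | −10% | 6.1% |

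The 15% / 5% case keeps overall loss at the planned level: 0.15 × 83 + 0.05 × 83 = 16.6, which is 10% of 166. For a change-score test, g is read in SDs of the change.

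**The case against.** The strongest reply is that the exception is disclosed. It stands in a sentence about factors with potential to bias, and the Trial design section also signals a departure from intention-to-treat. At the planned 10% loss the plausible bias is modest, and imputation details are commonly left to an analysis plan that is not shown. Most of this is fair. It does not remove the unqualified label in two other sections, and the exclusion is stated here, not left open.

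A reader might infer several stronger things that the documents do not support.

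- *That the result will be biased in favour of exercise.* No loss by arm and no outcomes of those lost are given. The bias may be nil or may run the other way.
- *That workers who cannot tolerate the sessions drop out of the analysis.* The rule keeps non-compliers. The pain and discomfort criteria in the exercise section stop the exercise, and nothing there withdraws anyone from assessment.
- *That the Discussion's real-world argument collapses.* That argument concerns workers who do not follow instructions, and such workers are retained if they return at 12 weeks.
- *That the comparison is valid only if data are missing completely at random.* Equal and equally selective loss in both arms cancels in the difference.
- *That the t test ignores baseline.* The Abstract describes a test on the change from baseline.

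**Conclusion.** The point holds as a mismatch between label and rule, with an unprotected exposure to selective loss. The article calls the analysis intention-to-treat and then excludes randomised participants lost to follow-up. Its four statements on the matter do not agree. The sample size allowance covers lost precision only.

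The size is conditional. Under assumed losses of 15% and 5%, the bias is 0.05 SD for a 0.5 SD gap and 0.10 SD for a 1 SD gap, that is 10% to 20% of the 0.5 design effect. It is zero if loss is unrelated to outcome, or equal and equally selective in both arms, and it reverses if selective loss falls mainly in the control arm. The mismatch is certain from the text. The direction and size of any bias are not.

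**What to change.** 1. In Statistical approach, delete the exception for those lost to follow-up. State that all randomised participants are analysed in their assigned arm, with missing 12-week values handled under a named assumption, for example multiple imputation by arm from the baseline outcome and the baseline characteristics already collected.
2. Remove or explain the deviation wording in Trial design, and align Sample size calculation and the Discussion with the same definition.
3. Add one delta-adjusted (tipping-point) sensitivity analysis for outcome-related loss. With no interim outcomes, imputation from baseline alone recovers little about those who leave, so this analysis matters more than the choice of imputation model.
4. Report losses and reasons by arm.
5. Seek the 12-week pain score and questionnaires remotely from people who do not attend. This cannot recover isokinetic torque or grip strength, which are also primary outcomes, so the sensitivity analysis is needed for those in any case.
6. Keep the available-case result, labelled as such, as a sensitivity analysis.

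The cost is wording, modest analysis work and some remote questionnaires. Estimates may be slightly wider or less favourable to exercise. The choice should be settled before outcomes are compared by arm, since missing-data choices made afterwards would be less credible.
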